## Abstract

**Background:**

Drug-drug interactions (DDIs) can cause patient harm. Between 46 and 90% of patients admitted to the Intensive Care Unit (ICU) are exposed to potential DDIs (pDDIs). This rate is twice as high as patients on general wards. Clinical decision support systems (CDSSs) have shown their potential to prevent pDDIs. However, the literature shows that there is considerable room for improvement of CDSSs, in particular by increasing the clinical relevance of the pDDI alerts they generate and thereby reducing alert fatigue. However, consensus on which pDDIs are clinically relevant in the ICU setting is lacking. The primary aim of this study is to evaluate the effect of alerts based on only clinically relevant interactions for the ICU setting on the prevention of pDDIs among Dutch ICUs.

**Methods:**

To define the clinically relevant pDDIs, we will follow a rigorous two-step Delphi procedure in which a national expert panel will assess which pDDIs are perceived clinically relevant for the Dutch ICU setting. The intervention is the CDSS that generates alerts based on the clinically relevant pDDIs. The intervention will be evaluated in a stepped-wedge trial. A total of 12 Dutch adult ICUs using the same patient data management system, in which the CDSS will operate, were invited to participate in the trial. Of the 12 ICUs, 9 agreed to participate and will be enrolled in the trial. Our primary outcome measure is the incidence of clinically relevant pDDIs per 1000 medication administrations.

**Discussion:**

This study will identify pDDIs relevant for the ICU setting. It will also enhance our understanding of the effectiveness of alerts confined to clinically relevant pDDIs. Both of these contributions can facilitate the successful implementation of CDSSs in the ICU and in other domains as well.

**Trial registration:**

Nederlands Trial register Identifier: NL6762. Registered November 26, 2018.

## Background

Drug-drug interactions (DDIs) are an important cause of adverse drug events (ADEs) [1]. In ICU patients, approximately 16% of all ADEs are caused by a DDI [2]. ADEs in the ICU are linked to increased length of stay, higher morbidity and mortality and increased hospital costs [3]. A DDI occurs when one or more drugs affect the pharmacokinetics (the body’s effect on the drug) and/or pharmacodynamics (the drug’s effect on the body) of one or more other drugs [4]. In the ICU, between 46 and 90% of the patients are exposed to a potential DDI (pDDI) [5]. This rate is twice as high compared to patients on general wards [6, 7]. A pDDI is defined as two potentially interacting medications administered concomitantly [8]. A pDDI may lead to an actual DDI, which could result in an ADE.

Studies have demonstrated the potential of clinical decision support systems (CDSSs) in preventing pDDIs [9, 10]. CDSSs focus on helping clinicians to improve their clinical performance. Computerized clinical decision support is defined as “providing clinicians or patients with computer-generated clinical knowledge and patient-related information, intelligently filtered or presented at appropriate times, to enhance patient care” [11]. A CDSS provides guidance at the point of prescribing by means of usually interruptive medication alerts that warn the prescriber for risky situations such as pDDIs [10]. However, the literature shows that there is considerable room for improvement, especially regarding the clinical relevance (and thereby the specificity) of the medication alerts generated by CDSSs [12–14]. Which pDDI alerts are generated by a CDSS depends on the underlying (sometimes commercial) knowledge base. [15] Lack of a fit between the clinical setting and the pDDI knowledge base used can be a cause of low specificity of medication alerts. Low specificity leads to alert fatigue and a high override rate of alerts. [16] Studies show that clinicians override alerts, including pDDI alerts, in 49 to 96% of the cases [16, 17]. These “side effects” of CDSS diminish the potential value of CDSSs for medication safety.

The ICU setting differs from other in- and outpatient settings for several reasons: patients in the ICU are more vulnerable for DDIs due to often-present impaired absorption, diminished renal and hepatic function, and polypharmacy [18]. On the other hand, as ICU patients are under continuous monitoring, some pDDIs are more acceptable than for non-ICU patients, because continuous monitoring allows for effective and timely risk management. Therefore, pDDI alerts that are clinically relevant in non-ICU settings may be of limited clinical value in the ICU. However, consensus on which pDDIs are clinically relevant in the ICU setting is lacking, and this hampers adequate pDDI alerting through CDSSs.

Therefore, the primary aim of this study is to evaluate the effect of tailoring pDDI alerts to the ICU setting on pDDI prevention among Dutch ICUs. To this end, we first identify which pDDIs are considered clinically relevant for the ICU setting through a standardized and rigorous Delphi procedure with a national expert panel. Next, we will use the resulting set of clinically relevant pDDIs as the ICU-specific pDDI knowledge base that a CDSS will use to generate alerts. Subsequently we will evaluate the effectiveness of this tailored strategy on the prevention of the clinically relevant pDDIs.

### Theoretical foundation

Alert fatigue can be described as “the mental state that is the result of alerts consuming too much time and mental energy, which can cause relevant alerts to be unjustifiably overridden along with clinically irrelevant ones” [16, 19]. Alert fatigue may lead to patient harm, when alerts pertinent to patient safety are overlooked and ignored [10]. To combat alert fatigue, it is important to optimize the balance between sensitivity and specificity of an alerting system [10, 12, 16]. The sensitivity of an alerting system is the ability of the system to produce an alert when that is necessary. When sensitivity is high, there are only few situations in which the system fails to provide an alert when it should have provided one. The specificity of an alerting system is the ability of the system to produce an alert, only if necessary. When the specificity is high, the system produces few unnecessary alerts (‘false alarm’) [13, 16]. To visualize sensitivity and specificity influencing alert fatigue and alert overrides, van der Sijs et al. [16, 20] applied Reason’s model of accident causation to drug-safety alerting and used this model to interpret how errors arise in an alerting system. The model is shown in Fig. 1.

**Fig. 1 Fig1:**
[figure not shown]
Adapted version Reason’s model of accident causation applied to drug safety alerting from van der Sijs et al. (with permission) [16, 20]

Lack of a fit between the clinical setting (e.g. ICU setting) and medication alerts is one cause of low specificity. Therefore, we hypothesize that using a pDDI knowledge base not tailored to the ICU setting, would lead to alert fatigue and thereby to ignoring pDDI alerts, as is depicted in Fig. 1. This in turn may result in also overriding clinically relevant pDDI alerts, compromising medication safety in the ICU. Therefore, to improve the specificity of pDDI alerts for the ICU setting, we first need to assess which pDDIs are clinically relevant for the ICU setting. A tailored pDDI knowledge base for the ICU setting will increase the specificity of pDDI alerts and reduce alert fatigue and pDDI alert overrides. This in turn will decrease the risk of ignoring relevant alerts, and eventually decrease the number of pDDIs.

## Methods/design

### Study design

To evaluate the effect of tailoring the pDDI knowledge base to the ICU setting on pDDI prevention we will implement a trial with a stepped-wedge design. A stepped-wedge trial is a type of cluster trial in which an intervention is rolled-out sequentially to the clusters over a number of periods that are called ‘steps’ [21]. By the end of the trial period, all clusters will have received the intervention. The order in which the clusters receive the intervention is randomized [22]. Data analysis to determine the overall effectiveness of the intervention subsequently involves comparison of the data points in the control section of the wedge with those in the intervention section [21].

We prefer a stepped-wedge design over a randomized controlled trial because withholding CDSS from those already using it is not considered ethical in our study. Withholding decision support in an environment where physicians are used to receive support to prevent pDDIs could have a negative effect on patient safety. Furthermore, methodologically speaking the stepped-wedge design is comparable to a parallel cluster RCT. Also, when the clusters are large, as is the case in our study, a stepped-wedge design is more powerful than a parallel design [23].

The order in which the ICUs will receive the intervention will be randomized, because randomization helps reduce the risk of bias and thereby increase the internal validity of the study [24]. An independent researcher who is not involved in further conduct of this study will perform the computerized randomization. As all the prescribing physicians in the participating ICUs and the investigators will be aware of the ‘step’ from control to intervention status, blinding is not feasible. Further details on the implementation of the stepped-wedge design in this study can be found in the paragraph ‘Stepped-wedge design implementation’.

This protocol is reported in accordance with the SPIRIT 2013 guideline for content of clinical trial protocols [25]. The results of this study will be reported in accordance with the CONSORT statement [26].

### Study setting

The setting of this study is the Dutch intensive care. In the Netherlands, all ICUs are mixed medical-surgical closed-format ICUs. All Dutch ICUs participate in the Dutch quality registry called National Intensive Care Evaluation (NICE). The NICE registry offers ICUs feedback and benchmarking on patient outcomes, including mortality, and allows them to compare their outcomes with those achieved nationally and by groups of similar hospitals [27].

To participate in our study, we require that an ICU department should use the commercial patient data management system, MetaVision ICU (*i*MD*Soft*®) during the whole trial. This is a pragmatic criterion, but one that allows a straightforward integration of the intended CDSS within this system. In particular, our CDSS will be obtained by adapting a current version of a CDSS that already works with MetaVision ICU but which provides pDDI alerts indiscriminately, hence regardless of clinical relevance for the ICU setting. In effect we need to replace the existing pDDI knowledge base in this CDSS to one which is tailored to the ICU setting. This essentially means that we will make a critical selection of the pDDIs for which the alerts should fire. By opting for one type of data management system and the CDSS that is able to operate within it, all participating ICUs will receive the pDDI alerts in the same manner. We invited all ICUs that use MetaVision, 12 in number, to participate in this study via the network of the NICE registry. Nine ICUs have agreed to participate in the trial and have provided an intensivist of the ICU as a local contact person. The remaining three ICUs decided not to participate in the trial because their hospital was in the process of migration to a different, hospital-wide, patient data management system. The nine participating ICUs have an overall capacity of 156 beds, and in total around 11200 (median: 854; IQR: 793–1785) patients are admitted yearly. One ICU is academic, eight are non-academic. The ICUs are geographically well distributed over the Netherlands.

The CDSS system that is compatible with MetaVision ICU, and available since January 2012, is the Medication Interaction Module (MiM, It*é*Medical®). The use of MIM within MetaVision ICU is optional. Five out of the nine participating ICUs already use MiM in Metavision ICU for four to six years before the start of the trial. The MiM can produce two types of medication alerts at the point of prescribing: pDDI alerts and duplicate orders alerts. Each ICU can set the (severity) level at which MiM provides alerts. The pDDI knowledge base integrated in MiM is the so-called G-standard. The G-standard is an evidence-based professional database for the management of medication alerts, developed and maintained by a working group of the Scientific Institute of Dutch Pharmacists. [8] The G-standard is used in most Dutch hospitals as the underlying knowledge base for decision support. For each pDDI, the working group assigns a severity and evidence level based on Summary of Product Characteristics and literature. Furthermore, the working group also provides a summary of interaction mechanism and recommendations on how to handle medication alerts (e.g. by monitoring of laboratory values). This situation is unique, as in many other countries, the development and maintenance of CDSS knowledge bases for medication are not organized at a national level. In the G-standard, medications are represented by generic product codes. The generic product code describes medication on the pharmaceutical level, based on the following pharmaceutical characteristics: active ingredients, strength, dosage form and route of administration [28]. All pDDIs are enlisted in the G-standard as pairs of generic product codes. The G-standard however originates from the outpatient setting and is not tailored to the ICU setting.

### Patient eligibility criteria

Patients over the age of 18 years admitted to the ICU having any administered medications during their ICU admission will be included.

### Establishing clinically relevant pDDIs

To determine which pDDIs are clinically relevant for the ICU setting, we will apply a modified Delphi procedure, in which an expert panel of intensivists and hospital pharmacists will assess the clinical relevance of pDDIs. The pDDIs to be assessed will be selected from the G-standard according to their frequency in the ICU and the assigned severity level. In essence, a pDDI is defined as clinically relevant for the ICU setting when non-standard monitoring for possible pDDI effects is required, or the pDDI should always be avoided. The modified Delphi procedure will be based on the RAND method [29], and will consist of an online questionnaire and expert panel meeting.

### Intervention

Our intervention consists of a version of the MiM that will only provide alerts for pDDIs considered clinically relevant in the ICU, according to our Delphi procedure. pDDI alerts considered not clinically relevant for the ICU will be turned off. This MiM version tailored to the ICU setting will be called MiM+. Our hypothesis is that alert fatigue can be reduced by MIM+, as the set of pDDIs for which alerts are provided at the point of prescribing, will be restricted and more specific for the ICU setting.

In the four participating ICUs that do not use the current MIM CDSS for pDDIs, the MiM+ software will be installed. Duplicate order alerts will not be shown in these four ICUs.

In the five ICUs that already use MiM as CDSS for pDDIs, MiM+ will start operating in these ICUs during the intervention phase. However, pDDI alerts not assessed during our Delphi procedure and for which an ICU gets alerts according to its current alert level setting, will not be changed. Furthermore, other types of alerts such as duplicate order alerts will also not be changed by our intervention. In short, the ICUs with a MiM CDSS will experience change in the alerts that were assessed in the Delphi rounds, in the sense that alerts for the pDDIs deemed irrelevant will be suppressed. All participating ICUs will receive an on-site training for the prescribing physicians about MiM+ given by a researcher involved in this study.

Apart from this intervention, all participating ICUs will receive two performance feedback rapports before MiM+ implementation. In these reports, results of a retrospective analysis of medication administration data on the occurrence of pDDIs will be included. The results will include pDDI occurrence over one year for the specific ICU, benchmarked against the other participating ICUs.

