### Statistical analysis

Depending on the distribution of variables, descriptive statistics will be presented as mean and standard deviation, median and IQRs, or percentage as appropriate. Continuous variables will be compared using the t-test or Mann-Whitney test. Categorical variables will be compared with a Chi squared test or Fisher’s exact test. To assess the effect of tailoring pDDI alerts to the ICU setting on the number of pDDIs per 1000 medication administrations we will analyse data from the stepped-wedge trial, adjusting for data clustering and for temporal trends if necessary. A generalized linear model will be fitted with correction for clustering via generalized estimating equations. To adjust for possible confounding patient characteristics (age and disease severity) and other variables (such as the previous use of MiM prior to MiM+) will be considered for addition in the model as covariates. We anticipate that most DDIs will occur around the third day of admission, because by that time chronic home medication often is restarted in the ICU while medication typically prescribed in the ICU is still prescribed [32].

All analyses will be performed according to the intention-to-treat principle. For hypothesis testing a probability level of less than 0.05 will be considered statistically significant. All statistical tests will be two-sided. The R statistical software environment will be used for the analyses.

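### The single pooled MiM+ estimate is labelled the effect of tailoring, but only five of the nine ICUs change from untailored to tailored alerts

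*Protocol article*

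**What the plan says.** All references are to the protocol article.

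- **Aim.** The Background section says that "the primary aim of this study is to evaluate the effect of tailoring pDDI alerts to the ICU setting on pDDI prevention". The abstract is broader. It sets out to "evaluate the effect of alerts based on only clinically relevant interactions for the ICU setting on the prevention of pDDIs among Dutch ICUs".
- **Starting points.** Under Study setting: "Five out of the nine participating ICUs already use MiM in Metavision ICU for four to six years before the start of the trial". Under Intervention: "In the four participating ICUs that do not use the current MIM CDSS for pDDIs, the MiM+ software will be installed".
- **What changes.** In the five MiM ICUs, alerts judged irrelevant in the Delphi procedure are switched off. Duplicate-order alerts continue there, as do "pDDI alerts not assessed during our Delphi procedure and for which an ICU gets alerts" at their current setting. In the other four, MiM+ is new and duplicate-order alerts are not shown.
- **Mechanism.** The Theoretical foundation and Intervention sections expect the benefit to come from less alert fatigue through a more specific alert set.
- **Analysis.** The Statistical analysis section describes the stepped-wedge result as the effect of tailoring, from a generalized linear model fitted by GEE. On prior use it says that "other variables (such as the previous use of MiM prior to MiM+) will be considered for addition in the model as covariates".
- **Sample size.** One average reduction of 20% is assumed for all participating ICUs, from a single event rate of 42.0 per 1000 administrations.

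**The concern.** Two different contrasts enter one coefficient. In five ICUs the contrast is MiM against MiM+, which is the tailoring question. In four it is no MiM against MiM+, which is the introduction of an alerting module. In those four, MiM alerts go up from none, so relief from untailored MiM alerts cannot be what acts there.

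A main-effect term for prior MiM use lets the two groups start from different pDDI rates. It still forces one MiM+ effect on both. The text names no interaction and no effect by group, and the limitations in the Discussion do not mention the two contrasts.

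At stake is the headline conclusion. A significant pooled result could come largely from first-time alerting and be reported as evidence that tailoring works. Conversely, a real tailoring effect could be diluted if introduction does little.

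**Working it through.** **Inputs (Sample size section).** 9 clusters, 10 periods, one switch per step, 600 administrations per cluster-period, rates 42.0 and 33.6 per 1000, ICC 0.12, two-sided Wald Z at 0.05. From Study setting and Intervention: 5 prior-MiM and 4 other ICUs.

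**Step 1: reproduce the stated power.** Model: fixed period effects and a random cluster intercept, analysed by generalised least squares on the rate-difference scale.

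- Total variance is the Poisson variance, 0.042.
- Between-cluster variance: 0.12 × 0.042 = 0.00504.
- Within-cluster variance of a cell mean: 0.88 × 0.042 / 600 = 0.0000616.
- SE of the pooled effect: 2.90 per 1000.
- Power = Φ(8.4/2.897 − 1.96) = Φ(0.94) = 82.6%.

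The protocol states 83%, so the model matches. That power is for one effect common to all nine ICUs.

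**Step 2: weight of each ICU in the pooled estimate.** By step, first to last: 0.055, 0.097, 0.127, 0.145, 0.151, 0.145, 0.127, 0.097, 0.054. They sum to 1, apart from rounding.

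Over all 126 placements of the five prior-MiM ICUs on nine steps, the four other ICUs together carry:

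- on average 4/9 = 44%;
- at least 30% (steps 1, 2, 8 and 9);
- at most 57% (steps 4, 5 and 6 with 3 or 7).

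**Step 3: what the pooled estimate would show.** Expected pooled reduction = (5/9) × tailoring effect + (4/9) × introduction effect. The documents give no effect by group, so the splits below are assumptions. Both groups are given the same control rate of 42.0.

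| Tailoring | Introduction | Expected pooled | Chance of significance |
|---|---|---|---|
| 20% | 20% | 20.0% | 83% |
| 10% | 32.5% | 20.0% | 83% |
| 0% | 45% | 20.0% | 83% |
| 0% | 29% | 12.9% | 46% |
| 0% | 20% | 8.9% | 25% |

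Fourth row: 0.129 × 42.0 = 5.41 per 1000, and Φ(5.41/2.897 − 1.96) = Φ(−0.09) = 46%. The protocol cites reductions of 15% to 29% for IT-based interventions, so 29% is the top of its own range. The first three rows give the same expected pooled result although tailoring contributes quite differently.

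**Step 4: separate effects.** The same model with shared period effects and one MiM+ effect per group, averaged over the 126 placements:

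| Estimate | SE per 1000 | Power for a 20% reduction |
|---|---|---|
| Pooled, nine ICUs | 2.90 | 83% |
| Prior-MiM ICUs, joint model | 3.40 | 69% (62–75%) |
| Other four ICUs, joint model | 3.66 | 63% (52–70%) |
| Five prior-MiM ICUs analysed alone | – | 54% (46–57%) |

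The tailoring SE is 3.40/2.90 = 1.17 to 1.18 times the pooled one. For a 15% reduction, power for tailoring is about 46% in the joint model and 34% from the five ICUs alone.

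**The case against.** The strongest reply is that the pooled effect does answer a question the protocol asks. The abstract's aim concerns alerts confined to clinically relevant interactions, and the intervention is defined as MiM+. An average effect of MiM+ over current practice, whatever that practice is, fits that aim. This stands, and it is why the pooled estimate need not be abandoned. It does not cover the narrower aim in the Background or the label in the Statistical analysis section.

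A reader might go further and infer three things that the documents do not support:

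- **That the trial cannot answer the tailoring question.** It can. The five prior-MiM ICUs supply that contrast.
- **That randomisation ignored prior MiM use.** The Study design section says only "The order in which the ICUs will receive the intervention will be randomized", by an independent researcher using a computer. Restriction or stratification is a detail an article may leave to the full protocol.
- **That the four ICUs had no pDDI alerts at all.** The text says they do not use MiM. Another alert source is neither stated nor excluded. Either way, their contrast is not MiM against MiM+.

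Two further replies carry some weight. The form of the covariate is not fixed, and an interaction could sit in an analysis plan that is not shown. But the article itself states one effect and calls it tailoring, so the point does not rest on an omission. Also, alert override data, the qualitative evaluation and the stated limitation on duplicate-order alerts bear on alert fatigue. They may help to explain a result, but they do not separate the two effects on the primary outcome.

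The 30–57% range is model-dependent. The ICUs differ in size (median 854 admissions yearly, IQR 793–1785), and no working correlation is fixed. Under independence weighting with period effects, the step weights are 0.300, 0.233, 0.175, 0.125, 0.083, 0.050, 0.025, 0.008 and 0. Four ICUs could then carry from 0.083 to 0.833.

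**Conclusion.** The concern holds as a mismatch between label and estimate. What is planned is the effect of introducing MiM+ across ICUs with two different starting points. Two sections call it the effect of tailoring, which only five of the nine ICUs can show. A significant pooled result is possible with no tailoring effect.

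The average weight of 44% on the newly equipped ICUs follows from four ICUs out of nine of equal size. The 30–57% range also needs the exchangeable model that reproduces the stated power. The chances of significance in the no-tailoring scenarios, 25% to 46%, further need the assumed group effects and a common control rate. All power figures are z-based with nine clusters and so are optimistic.

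The defect lies in what is claimed from the pooled estimate. The design and the data can still inform tailoring.

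**What to change.** 1. Keep the pooled estimate as primary, and name it the effect of introducing MiM+ over mixed usual practice. Bring the aim in the Background and the sentence in the Statistical analysis section into line with the abstract.
2. Prespecify a MiM+ by prior-MiM-use interaction alongside the main effect of prior use. Report the MiM+ effect in each group with a confidence interval.
3. Base any statement about tailoring on the effect in the five prior-MiM ICUs.
4. Say whether the four ICUs had another source of pDDI alerts before MiM+.
5. Only if randomisation is still open and this is not already done, spread the two groups over early, middle and late steps.

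**Cost.** One model term and a narrower claim. The tailoring estimate has an SE about 18% larger than the pooled one. Its power for a 20% reduction is about 69% with period effects shared across groups and about 54% from the five ICUs alone. The protocol should state this, so that a non-significant tailoring effect is not read as evidence of none.
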